## Abstract

**Background:**

Triple negative breast cancer (TNBC) accounts for 10-20% of breast cancers but has no specific therapy. While TNBC may be more sensitive to chemotherapy than other types of breast cancer, it has a poor prognosis. Most TNBC relapses occur during the five years following treatment, however predictive biomarkers of metastatic relapse are still lacking. High tumour-infiltrating lymphocytes (TILs) levels before and after neo-adjuvant chemotherapy (NAC) are associated with lower relapse risk and longer survival but TILs assessment is highly error-prone and still not introduced into the clinic. Therefore, having reliable biomarker of relapse, but easier to assess, remains essential for TNBC management. Searching for such biomarkers among serum/plasma proteins, circulating tumoral DNA (ctDNA) and blood cells appear relevant.

**Methods:**

This single-centre and prospective study aims to discover predictive biomarkers of TNBC relapse and particularly focuses on plasma proteins. Blood samples will be taken at diagnosis, on the day of first-line or post-NAC surgery, on the day of radiotherapy start, then 6 months and one year after radiotherapy. A blood sample will be taken at the time of metastatic relapse diagnosis. Blood samples will be used for circulating protein quantification, blood cell counts and circulating tumour DNA quantification. A tumour RNA signature, based on the analysis of the RNA expression of 6 genes, will also be tested from the initial biopsy taken routinely. In NAC patients, TILs quantity will be assessed on TNBC pre-treatment biopsy and surgical specimen.

**Ethics and Dissemination:**

INSTIGO belongs to category 2 interventional research on humans. This study has been approved by the SUD*-*EST IV ethics committee and is conducted in accordance with the Declaration of Helsinki and General Data Protection Regulation (GDPR). Study findings will be published in peer-reviewed medical journals.

**Clinical Trial Registration:**

ClinicalTrials.gov, identifier NCT04438681.

## Introduction

Triple negative breast cancer accounts for approximately 10-20% of breast cancers and is characterized by the lack -or by very low - expression of oestrogen and progesterone receptors and the lack of amplification of the gene coding for HER2 (Human Epidermal Growth Factor Receptor 2) (1). TNBC has no specific therapy; chemotherapy, radiotherapy and surgery remain preferred modalities. While TNBC may be more sensitive to chemotherapy than other types of breast cancer, it has a poor prognosis due to its heterogeneity (2–4). Predictive biomarkers of metastatic relapse and type of relapse need to be discovered. Among these predictive biomarkers, it has been shown that a high level of TILs before and after NAC is associated with lower recurrence risk and longer recurrence-free survival (5, 6). However, TIL assessment is error-prone and subject to high inter-evaluator variability despite the existence of standardized recommendations (7, 8). It is also known that a complete pathological response to NAC is associated with a low risk of metastatic relapse in TNBC (9). The determination of biomarkers that are easily quantifiable at diagnosis is essential. The search for predictive biomarkers of metastatic progression among circulating molecules seems relevant (10, 11). It has been shown that high concentrations of proteins involved in inflammation, such as interleukins 6 and 8, or involved in angiogenesis, such as angiopoietin-like protein, are associated with a high risk of metastatic progression of breast cancer (12–14). In TNBC, high blood levels of transforming growth factor-β (TGF-β) and vascular endothelial growth factor-A (VEGF-A) are associated with a high risk of relapse (15). Circulating proteins assays are part of routine clinical testing and have a high sensitivity. Targeted analysis of the blood proteome (serum/plasma), using high throughput techniques such as multiplex ELISA, appears to be an interesting approach for the discovery of new biomarkers. In this context, we propose to conduct a study that measures the concentrations of a set of plasma proteins to evaluate their ability to predict metastatic relapse in patients with TNBC.

The interest in circulating biomarkers also leads us to focus on blood cells which are easily quantifiable and accessible. Blood cells and their ratios [Platelet-to-lymphocyte Ratio (PLR) and Neutrophil-to-lymphocyte Ratio (NLR)] are predictive and prognostic biomarkers of breast cancer (16, 17). In patients with TNBC, a high NLR, reflecting a weak immune response, is associated with a poor response to NAC and a poor survival (18, 19). In addition, plasma from cancer patients contains circulating tumoral DNA (ctDNA) carrying tumour mutations. ctDNA is proving to be another biomarker of interest to study. ctDNA levels make it possible to anticipate the response to treatment and to predict the risk of metastatic relapse (20, 21). They are also a predictive and prognostic biomarker in patients with metastatic breast cancer (22). Combining the characteristics of a plasma protein profile, blood cells levels (PLR, NLR) and ctDNA would provide information on the metastatic potential of a given tumour.

Finally, analyses of tumour RNA expression of a wide range of genes by PAM50 tests, EndoPredict tests, MammaPrint tests or even BluePrint tests allow clinicians to classify breast cancers into molecular subtypes, each corresponding to a specific prognosis and treatment proposal (23–27). However, no such tests exist for TNBCs. The validation of an RNA signature of triple negative breast tumours, established at the Centre Jean Perrin by the analysis of the RNA expression of 6 genes, could provide us an indication on the treatments to be preferred.

## Methods and Study Design

### Study Design

This is a single-centre prospective trial designed to evaluate a plasma protein profile as a predictive biomarker for metastatic relapse of TNBC. The estimated duration of patients’ enrolment is 3 years: 90 patients will be enrolled and followed from the patient inclusion until the first metastatic relapse or up to 5 years after the end of treatment if no relapse occurs. Study design is presented in **Figure 1**. TNBC patients will have blood samples taken at diagnosis, on the day of first-line surgery or post-NAC surgery, on the day of radiotherapy start, and 6 months and one year after the end of radiotherapy. Patients receiving neoadjuvant radiation will not be included in the trial. In case of recurrence, a blood sample will be taken at the time of diagnosis of metastatic relapse. Blood samples will be used for the quantification of plasma proteins, for the determination of blood cells and for the quantification of ctDNA. TILs rate evaluation will be performed on tumour tissue from the biopsy and from the operating specimen. The quantification of proteins will be done by multiplex ELISA. The identification of tumoral DNA mutations will be made from extracted DNA from tumour tissue from the operating specimen or from the biopsy. All coding regions, including exons borders and splicing sites, of the ten most frequently muted genes in breast tumours (including TP53, PTEN, PIK3CA, etc) will be captured from sample genomes. Then, targeted regions will be analysed by high throughput sequencing. Targeting several genes will ensure to discover at least one tumour-specific mutation. This mutation will later be quantified in peripheral blood samples. The RNA signature will be generated from transcripts extracted from tumour tissue from the surgical specimen or from the biopsy. A multiplex RT-qPCR will quantify the expression levels of the 6 genes of interest. The expression level of each gene will be multiplied by the corresponding coefficient in order to generate a prognostic score.

**Figure 1 f1:**
[figure not shown]
Design of the INSTIGO study. Patients will have blood samples taken at diagnosis, on the day of first-line surgery or post-NAC surgery, on the day of the start of radiotherapy, and 6 months and one year after radiotherapy. If necessary, a blood sample will be taken at the time of diagnosis of metastatic relapse. Blood samples will be used for circulating proteins quantification, blood cells assay and circulating tumour DNA quantification. In neoadjuvant setting, TILs rate will be evaluated from tumour tissue from the biopsy and from the operating room.

### Study Objectives

The primary objective of the INSTIGO trial is to discover a baseline plasma protein profile predictive of metastatic relapse in patients with TNBC (**Table 1**). It also aims to identify a plasma protein profile at different times during patient follow-up that could be predictive of metastatic relapse. Based on a review of the literature INSTIGO focuses on a specific group of proteins: Matrix metalloproteinase 9, tissue inhibitor of metalloproteinase 1, interleukin-6, interleukin-8, interleukin-10, programmed death-ligand 1, stromal cell-derived factor 1, GM-CSF, tyrosine kinase with immunoglobulin and epidermal growth factor-homology domains 2, TGF-β, VEGF-A, hepatocyte growth factor, fibroblast growth factor, CXCL5, CXCL12. Moreover, the INSTIGO study takes interest in others potential biomarkers such as ctDNA, blood cells, TILS, or tumour RNA expression (**Table 1**). Briefly, the objective is to evaluate the ability of those potential biomarkers to predict metastatic relapse in patients with triple-negative breast cancers.

**Table 1 T1:** Primary and secondary objectives.

Primary objective	To discover a baseline plasma protein profile predictive of metastatic relapse in patients with TNBC
Secondary objectives	To discover plasma protein profiles predictive of metastatic relapse in patients with TNBC, assessed at - the day of first surgery or post-CTNA surgery - the day of the radiotherapy start - 6 months and one year after radiotherapy
	To study the relationship between the quantity of tumour infiltrating lymphocytes at diagnosis and metastatic relapse
	To study the relationship between NLR and PLR and metastatic relapse, when those 2 parameters are assessed at - diagnosis - the day of first surgery or post-CTNA surgery
	To study the relationship between plasma levels of circulating tumoral DNA and metastatic relapse - at diagnosis - at the day of first surgery or post-CTNA surgery - at the day of the start radiotherapy start - 6 months and one year after radiotherapy
	To verify prognostic value of a baseline RNA signature
In neoadjuvant setting	To identify a baseline plasma protein profile predictive of histological response to neoadjuvant chemotherapy (NAC)
	To study the relationship between variation in protein concentration, between diagnosis and end of NAC, and histological response to NAC
	To study the relationship between TIL quantity before and after NAC, as well as between the relationship between the baseline TIL level and the level of histological response to NAC
	To study the relationship between the variation of the PLR ​​and the NLR before and after NAC, as well as between the relationship between the baseline PLR and NLR levels and the level of histological response to NAC

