### Patient Selection

Inclusion and exclusion criteria are presented in **Table 2**. Briefly, women (18 years or older) with newly diagnosed, histologically proven and never treated primary triple negative breast cancer, and non-metastatic (M0) at diagnosis, will be included.

**Table 2 T2:** Inclusion and non-inclusion criteria.

Inclusion criteria	Female Age ≥ 18 years Newly diagnosed, histologically proven and never treated primary triple negative breast cancer, and non-metastatic (M0) at diagnosis Speaking and understanding French Affiliated to the French Social Security System Able to give informed consent.
Non-inclusion criteria	Patient deprived of liberty by court or administration decision In neoadjuvant situation: neoadjuvant treatment by radiotherapy or hormone therapy Refusal to participate to the study

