#### Secondary Analysis

To identify a plasma protein profile that is predictive of metastatic relapse, the same approach as for the main objective will be used.

The relationship between TILs, NLR and PLR levels measured at different times, or ctDNA plasma levels and metastatic relapse will be studied by Wilcoxon-Mann-Whitney tests and logistic regressions. Mixed models will be used to account for repeated data.

The relationship between, on the one hand, the variation in protein concentration, the variation in TILs, or the variation in PLR and NLR levels, between diagnosis and end of NAC, and, on the other hand, the histological response to NAC, will be studied as in the previous point. These aspects are also concerned by an intermediate analysis on the first 30 patients.

An RNA signature predictive of metastatic relapse will be assessed by applying a previously constructed model on the data obtained in the INSTIGO study. The classical indices for the evaluation of a classification (sensitivity, specificity, and precision, among others) will be calculated.

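### The surgery-day draw pools untreated and post-chemotherapy patients, and the stated secondary analyses have no term or stratum for treatment route

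*Protocol article*

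**What the plan says.** Study Design places one blood draw "on the day of first-line surgery or post-NAC surgery". Table 1 (Study Objectives) words this time point as "the day of first surgery or post-CTNA surgery" and uses it for three secondary objectives on metastatic relapse: the protein profile, NLR and PLR ("To study the relationship between NLR and PLR and metastatic relapse, when those 2 parameters are assessed at" diagnosis and this draw), and ctDNA. All three stand in the all-patient part of the table, apart from the rows for the neoadjuvant setting.

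Patient Selection admits women with "newly diagnosed, histologically proven and never treated primary triple negative breast cancer, and non-metastatic (M0) at diagnosis". At the surgery draw, therefore, one group has had no systemic treatment and the other has completed NAC.

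Under Secondary Analysis, later protein profiles follow the primary approach: per-protein Wilcoxon-Mann-Whitney tests with FDR control, then an elastic-net logistic model whose candidate variables are the proteins. For the other markers the section states: "The relationship between TILs, NLR and PLR levels measured at different times, or ctDNA plasma levels and metastatic relapse will be studied". The methods it names there are logistic regression and the Wilcoxon-Mann-Whitney test, with mixed models to handle repeated data. No route term or stratum appears in any of these. Data Collections does list treatments received, so route is available.

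**The concern.** One label covers two treatment states. The article expects the markers to move between them. Table 1 has an objective "To study the relationship between variation in protein concentration, between diagnosis and end of NAC, and histological response to NAC", and another on the variation of PLR and NLR "before and after NAC, as well as between the relationship between the baseline PLR and NLR levels". For ctDNA there is no matching objective, but the Introduction says that its level helps to anticipate treatment response.

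The approach suits the diagnosis draw, where nobody has been treated, but it is carried unchanged to a draw where treatment state differs. Two things can follow:

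- **Dilution.** A NAC shift adds between-route spread unrelated to relapse, and this weakens a real marker. It needs no link between route and relapse.
- **Standing in for route.** If relapse risk differs by route, a shifted marker is associated with relapse through route alone. It can be selected although it separates relapsers from non-relapsers within neither route.

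With about 30 relapses expected (90 × 1/3, from Sample Size Calculation), there is little power to spare.

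**Working it through.** **The plan's own figure.** The article gives no figure for the surgery draw. Its precision statement supplies the sample size and event count: 90 patients and 1/3 relapsing give 30 relapses. At 90% sensitivity (27 of 30) the 95% Wilson interval is 0.744 to 0.965, half-width 0.111, close to the rough ±12% stated. Nothing below depends on that width.

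**Inputs.** From the article: n = 90, relapse about 1/3. Assumed, because the article gives none of them: NAC share (50%, or 40–60%), marker shift after NAC (0, 1 or 1.5 within-route SD), true effect (0 or 0.62 SD), and relapse risk by route. The test is one two-sided Wilcoxon-Mann-Whitney test at 5%, without FDR correction or elastic-net selection.

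**Dilution, equal relapse risk by route.** With half the patients shifted by s, the pooled SD is √(1 + s²/4), so the standardised effect becomes 0.62/√(1 + s²/4):

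- s = 0: 0.62
- s = 1: 0.62/1.118 = 0.555
- s = 1.5: 0.62/1.25 = 0.496

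A normal approximation with 30 and 60 patients has non-centrality d × √(30 × 60/90) = 4.472d. Power is Φ(4.472d − 1.96): about 79%, 70% and 60%. Simulation of the rank test itself, with random group sizes, gives slightly lower values:

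| Shift after NAC | Pooled test | Stratified by route (van Elteren) |
|---|---|---|
| 0 SD | about 75% | about 75% |
| 1 SD | about 66% | about 75% |
| 1.5 SD | about 54% | about 75% |

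Repeat runs differ by a point or two.

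**Standing in for route, no effect within either route, 1 SD shift.** The pooled mean difference between relapsers and non-relapsers equals the shift times the difference in their NAC shares. At a 50% NAC share:

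- 45% vs 20%: 0.225/0.325 − 0.275/0.675 = 0.692 − 0.407 = 0.285 SD
- 40% vs 25%: 0.200/0.325 − 0.300/0.675 = 0.615 − 0.444 = 0.171 SD
- 35% vs 30%: 0.175/0.325 − 0.325/0.675 = 0.538 − 0.481 = 0.057 SD

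Simulated rejection at a nominal 5%, NAC share 40–60%:

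| Relapse, NAC vs first-line surgery | Pooled test |
|---|---|
| 45% vs 20% | about 18–21% |
| 40% vs 25% | about 8–10% |
| 35% vs 30% | near 5% |

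The stratified test stays at about 4–5% throughout. When relapse risk is equal by route, the pooled test also rejects about 5% of the time.

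**The case against.** **Silence is not pooling.** The article condenses a longer protocol that is not shown. It lists no covariates for any analysis, the logistic regressions could carry a route term, and an unseen analysis plan may add one. This stands as a limit on certainty. It does not remove the point, because the article itself defines the combined time point as an all-patient objective and names a two-group rank test and a proteins-only model, neither of which has a place for route.

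**Confounding is not documented.** A reader might infer that NAC goes to patients with more extensive disease, so that route must predict relapse. No section gives the criteria for NAC, the NAC share or relapse by route. The excess-selection half is therefore conditional and vanishes when the risks are close. The dilution half does not need this premise.

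**The shift is assumed.** Planning to study change over NAC anticipates a shift, but not one of 1 SD in every marker. This is granted; the figures are illustrations.

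**The 18–21% is not a type I error in the strict sense.** Where risk differs by route, a shifted marker really is associated with relapse marginally. The figure shows how often a marker with no value beyond route would be flagged. Nor does a single unadjusted test describe FDR-corrected tests or elastic-net selection.

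**Wider readings.** Two are tempting. One is that the draw at radiotherapy start has the same defect; the article does not describe chemotherapy after surgery, so this cannot be shown. The other is that route calls for separate profiles or a survival model; with about 30 relapses, separate fits would divide already scarce events, and this point gives no reason to abandon logistic regression.

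**Conclusion.** The point holds for the secondary objectives at the surgery-day draw: protein profile, NLR/PLR and ctDNA. As described, pooled marker values can partly reflect treatment route. If NAC shifts a marker by 1 to 1.5 SD, the illustrative loss is roughly 9 to 21 points of power (75% to 66% or 54%), and stratification avoids it. Excess selection of markers with no value within route ranges from none to about four times the nominal 5%, depending on a risk difference that the article does not give.

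The primary objective uses the diagnosis draw, before any treatment, and is untouched. A change is worth making because the needed data are already collected and, at publication, only 2 patients had been recruited, so it could be fixed before outcomes accrue.

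**What to change.** For the surgery-day draw:

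- Replace the pooled Wilcoxon-Mann-Whitney tests with rank tests stratified by route (van Elteren), keeping the FDR control for proteins.
- Add route (NAC or first-line surgery) as a covariate in the logistic and mixed models.
- In the elastic-net, standardise proteins within route and enter route as an unpenalised term. Do the standardisation inside each cross-validation fold.
- Describe the markers separately by route, but do not fit a separate elastic-net per route.
- Keep the planned logistic analysis.

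Apply the same route term to later draws as a precaution.

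The cost is analysis wording and one degree of freedom per model, or a few more in a mixed model across draws if the route term may differ by draw. No new data, visits or samples are needed. The result must then be read as prognostic value beyond route, which is narrower than overall predictive value, and the report should say so.

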### Patient Selection

Inclusion and exclusion criteria are presented in **Table 2**. Briefly, women (18 years or older) with newly diagnosed, histologically proven and never treated primary triple negative breast cancer, and non-metastatic (M0) at diagnosis, will be included.

**Table 2 T2:** Inclusion and non-inclusion criteria.

Inclusion criteria	Female Age ≥ 18 years Newly diagnosed, histologically proven and never treated primary triple negative breast cancer, and non-metastatic (M0) at diagnosis Speaking and understanding French Affiliated to the French Social Security System Able to give informed consent.
Non-inclusion criteria	Patient deprived of liberty by court or administration decision In neoadjuvant situation: neoadjuvant treatment by radiotherapy or hormone therapy Refusal to participate to the study

### Recruitment and Consent

Eligible patients will be offered the opportunity to participate in the study by their oncologist or their surgeon. Patients who agree to participate in this study will provide written informed consent for enrolment. Data obtained will be retained with consent, and any reasons given for withdrawal will be recorded. Participants can withdraw at any time.

### Sample Size Calculation

Given the exploratory nature of the study, and the lack of sufficient data to provide hypotheses in order to perform sample size calculation, the objective is to recruit a maximum of patients. The recruitment capacity for this study is estimated at 90 patients (30 patients per year). An interim analysis at 30 patients will allow us to re-evaluate the recruitment capacity, and to assess the interest of extending the recruitment period, and to re-estimate the number of subjects needed in view of the amount of missing data and the variability of the protein data. A rough estimation allows us to evaluate that with a sample size of 90 patients we would obtain a 95% (Wilson’s) confidence interval for the sensitivity of a 90% predictive score, with a precision of +/- 12%, assuming that the proportion of metastatic relapses at 5 years will be 1/3.

### Data Collections

Data collected are the patient’s age (month and year of birth), pathology, treatments received, response to NAC, clinical and molecular characteristics of the tumour on biopsy and surgical specimen and blood tests at diagnosis, on the day of the first-line surgery, before the start of radiotherapy, 6 months and 1 year after the end of radiotherapy and at the time of metastatic relapse. Data collected will be pseudonymized. Thus, study data will not contain any names or other personal identifiers such as addresses. Patients included in the trial will be identified by a code specific to this trial. The investigator will have access to the correspondence table between the patient’s last name, first name, date of birth and the code assigned in the trial.

